### *Retention*

Multiple strategies were implemented to increase retention in the study. First, participants were called up to five times for reminders of appointments. They were contacted by their preferred method of communication (email, text, phone, mail). Culturally-appropriate recruitment, retention, and engagement strategies were used based on previous studies on Puerto Ricans and similar Latino heritages, including showing familiarity, trust, and respect; obtaining at least three means of contact; sharing the participant’s clinical results in a simplified letter along with guidelines for clinically-acceptable values for consultation with their doctor; reimbursing transportation expenses or providing free transportation to/from FDI; providing snacks after each visit; allowing for flexible appointments (including weekends) and completion by phone; and using appropriate literacy level of materials and questionnaires [[98], [99], [100]]. During the 2019 earthquakes and the COVID-19 pandemic, participants received information on free or low-cost services, including mental health, and instructions for remaining in contact with the study. The value of their participation to scientific knowledge and future population health was also highlighted. These strategies benefited participants, even when there were no direct benefits from participating in the study.

### Statistical Analysis

Table 4 shows the minimum detectable effect sizes estimated for primary and secondary outcomes for the original sample size (n = 100) and adjusted sample size after COVID-19 protocols (n = 50), accounting for 10% loss-to-follow-up, using ANCOVA test [101] with 0.05 Type I error and 80% power.

**TABLE 4 tbl4:** Minimum detectable effect sizes (4 mo means adjusted for baseline) for primary and secondary outcomes for PROMED, using ANCOVA test for 80% power and 5% Type I error rate

	Mean (SD) at baseline	Empirical Corr. b∖w baseline and 4 mo values	MDE for n = 90 (45 per arm)	MDE for n = 44 (22 per arm)
10-item cardiometabolic improvement score	5.4 ± 1.4	0.94	0.28	0.40
Weight (lbs.)	201.2 ± 42.3	0.97	6.07	8.68
Waist circumference (cm)	42.9 ± 4.9	0.92	1.13	1.62
BMI (kg/m^2^)	34.2 ± 6.6	0.86	1.99	2.84
Systolic BP (mmHg)	123.4 ± 17.1	0.80	6.06	8.66
Diastolic BP (mmHg)	80.4 ± 9.3	0.49	4.79	6.85
Total cholesterol (mg/dL)	196 ± 46.5	0.59	22.17	31.71
LDL-C (mg/dL)	123.4 ± 37.4	0.83	12.32	17.62
HDL-C (mg/dL)	48.9 ± 12.4	0.83	4.08	5.84
Triglycerides (mg/dL)	118.2 ± 73.0	0.74	28.99	41.47
Glucose (mg/dL)	101.6 ± 29.4	0.80	10.42	14.90
Hemoglobin A1c (%)	6.0 ± 1.3	0.77	0.49	0.70
Diet quality (score)	35.2 ± 3.7	0.85	1.15	1.65
Diet satisfaction (score)	94.9 ± 18.9	0.85	5.88	8.41

BP, blood pressure; PROMED, Puerto Rican Optimized Mediterranean-like Diet. ∗The results account for 10% loss-to-follow-up for original sample sizes of n = 100 and n = 50. ∗∗The minimum detectable effect sizes (MDE) by the ANCOVA approach is calculated based on $MDE=\frac{4{\left(Z_{1-\frac{\alpha }{2}}+Z_{\beta }\right)}^{2}\left(1-Corr^{2}\right)SD^{2}}{n}$, where n is the sample size (active arm + control arm) after accounting for loss-to-follow-up, Corr is the correlation coefficient between the baseline and 4 mo values, SD is the standard derivation for the baseline value, $Z_{\tau }$ is the $\tau^{th}$ lower-quantile of the standard normal distribution, α=0.05 is the type I error rate, and β=0.8 is the power.

The primary analysis is intention-to-treat. Data analysis will follow the Consolidated Standards of Reporting Trials (CONSORT) guidelines [102]. Flowcharts will include the number of participants at each stage, including screened, eligible, randomized, and followed-up. At the 4-mo follow-up, the mean cardiometabolic improvement score for participants in the intervention arm versus the control arm will be compared using a two-sample *t*-test. If randomization does not control for differences between the treatment and control groups on baseline characteristics, those differences will be statistically controlled for using multivariable regression modeling. Secondary analysis will compare the change in individual cardiometabolic risk factors and dietary and psychosocial factors between intervention and control groups using an ANCOVA test. Repeated measures analysis will test differences in 2- and 4-mo outcomes. Prespecified subgroup analyses will be conducted by sex-at-birth, BMI status, pre-existing cardiometabolic profile, COVID-19 period (pre- vs. at-pandemic), and adherence status. Missing data and loss to follow-up will be corrected. Two-sided 0.05 type I error threshold for statistical significance will be used.

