### Primary and secondary outcomes

Similar to a previous study [31], the primary outcome of PROMED was a composite cardiometabolic improvement score representing the summed number of improved cardiometabolic risk factors out of the 10 factors that were part of the eligibility criteria; the score has a plausible range of 0–10. Improvement was defined by clinically-meaningful decreases of *1*) waist circumference ≥ 1 cm; *2*) BMI ≥ 1 kg/m^2^; *3*) systolic blood pressure ≥ 5 mmHg; *4*) diastolic blood pressure ≥ 5 mmHg; *5*) plasma glucose ≥ 1 mg/dL; *6*) hemoglobin A1c ≥ 0.5%; *7*) plasma triglycerides ≥10 mg/dL; *8*) total cholesterol ≥ 10 mg/dL; and *9*) LDL-C ≥ 10 mg/dL; or an increase of [8] HDL-C ≥ 5 mg/dL [[32], [33], [34], [35], [36], [37], [38], [39], [40]]. A composite score was selected to account for baseline variability in cardiometabolic risk profiles. Furthermore, the selected markers are routinely measured in standard laboratory tests, and the predefined improvements are clinically meaningful in reducing the risk of chronic disease, facilitating the potential for clinical translation.

Secondary outcomes included changes in the individual cardiometabolic risk factors plus weight, dietary intake, overall diet quality, diet satisfaction, dietary behaviors, and psychosocial factors (e.g., depressive symptoms, stress). An exploratory aim was conducted to assess changes in the gut microbiome profile, based on previous literature suggesting associations between a MedDiet, legumes and oils, and gut microbiota composition and microbial functions [[41], [42], [43], [44]].

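### Table 4's minimum detectable effect for the primary outcome (0.40 items at n = 44) rests on a baseline-adjusted ANCOVA that cannot apply to the improvement score and is not the planned primary test

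*Protocol article*

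**What the plan says.** Three places in the protocol article bear on this.

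- **Endpoint** (Primary and secondary outcomes). The primary outcome is the "summed number of improved cardiometabolic risk factors out of the 10 factors that were part of the eligibility criteria". A factor counts as improved when it has moved by at least a set amount, and the score runs from 0 to 10.
- **MDE** (Statistical Analysis, Table 4). The MDEs are computed "accounting for 10% loss-to-follow-up, using ANCOVA test [101] with 0.05 Type I error and 80% power". The row labelled "10-item cardiometabolic improvement score" has a baseline mean and SD of 5.4 ± 1.4, a correlation of 0.94, and MDEs of 0.28 (n = 90, 45 per arm) and 0.40 (n = 44, 22 per arm). The table footnote defines the correlation ("Corr is the correlation coefficient between the baseline and 4 mo values") and says of the spread that "SD is the standard derivation for the baseline value".
- **Primary test** (Statistical Analysis, text after Table 4). The planned primary comparison is a t-test: "At the 4-mo follow-up, the mean cardiometabolic improvement score for participants in the intervention arm versus the control arm will be compared using a two-sample". Multivariable regression follows only if the arms differ on baseline characteristics. ANCOVA is named for the secondary outcomes. The level is fixed: "Two-sided 0.05 type I error threshold for statistical significance will be used".

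**The concern.** The score is built from change since baseline. Before follow-up there is nothing to count, so it can have neither a baseline mean nor a correlation between baseline and 4 months. The 5.4 and the 0.94 must describe something else, and the article does not say what.

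The test also differs. A two-sample t-test of the 4-month score has no baseline covariate, so it does not gain the variance reduction that ANCOVA takes from a correlation of 0.94. That reduction produces most of the apparent precision in this row.

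Table 4 is the article's only statement of sensitivity for its primary outcome. It is also where a reader sees what the cut from 100 to 50 participants costs, apparently a move from 0.28 to 0.40 items. A reader who takes the row at face value would believe that the trial could detect a difference of less than half an item out of ten.

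**Working it through.** **Inputs from the article.** Two-sided α = 0.05 and power 80%, so z₀.₉₇₅ + z₀.₈₀ = 1.960 + 0.842 = 2.802. SD = 1.4 and r = 0.94 (Table 4, first row). n = 44 or 90, with equal arms.

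**Step 1: reproduce the table.** Use MDE = 2 × 2.802 × SD × √(1 − r²) / √n.

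- √(1 − 0.94²) = 0.341
- n = 44: 2 × 2.802 × 1.4 × 0.341 / √44 = 0.403 (table: 0.40)
- n = 90: 2 × 2.802 × 1.4 × 0.341 / √90 = 0.282 (table: 0.28)

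The other 13 rows reproduce to rounding in the same way, so the table was computed consistently. The fault in the first row lies in its inputs and the assumed test.

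**Step 2: remove the baseline term, as the planned test does.** Keep SD = 1.4 for the moment.

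- Normal approximation: 2 × 2.802 × 1.4 / √44 = 1.18, and 2 × 2.802 × 1.4 / √90 = 0.83
- Noncentral t: 1.21 with 22 per arm (42 df) and 0.84 with 45 per arm (88 df)

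The increase is by a factor of 1 / 0.341 = 2.93.

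**Step 3: power of the t-test at the tabulated MDEs, SD 1.4** (noncentral t).

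- 0.40 with 22 per arm: 15.1%
- 0.28 with 45 per arm: 15.3%

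**Step 4: vary the SD.** The SD of 1.4 is labelled a baseline SD and comes from the row whose inputs are in question. The article gives no SD for the improvement count, so the range below is an assumption (noncentral t throughout).

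| Assumed SD | MDE, 22 per arm | MDE, 45 per arm | Power at 0.40, 22 per arm |
|---|---|---|---|
| 1.0 | 0.865 | 0.597 | 25% |
| 1.4 | 1.211 | 0.836 | 15% |
| 2.0 | 1.729 | 1.194 | 9% |

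For the t-test to have an MDE of 0.40 at 22 per arm, the SD of the count would have to be about 0.46 items, on a scale from 0 to 10.

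**Step 5: the printed formula.** As it stands in the Table 4 footnote it has no square root. Taken literally at n = 44 it gives 0.163 for the score and 75.1 mmHg for systolic blood pressure, against tabulated values of 0.40 and 8.66. The tabulated values already include the root.

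**The case against.** The strongest objection is to naming a replacement figure. A reader might infer that the true MDE is 1.2 items, that it is three times the stated one, and that power is 15%. The article does not support that as a fact. If 5.4 and 0.94 cannot belong to the improvement score, the 1.4 beside them may not either. It might describe, for example, a count of risk factors present, but the article does not say so. This objection stands: 1.2 is an illustration conditional on SD 1.4. It does not rescue 0.40, because every SD from 1.0 to 2.0 gives more than twice that value.

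A second objection is that regression adjustment is also planned. It is conditional on imbalance in baseline characteristics, and it cannot restore r = 0.94 because there is no baseline score to adjust for.

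A third is that this is a pilot and feasibility trial, cut to 50 participants for budget and time, with sample size already listed as a limitation. That is fair. A reader might also infer that the trial was designed around an effect of 0.40, or that its conclusions depend on that figure. Neither is in the text: 0.40 is a reported MDE, no target effect is named, and misreading of a null result is a risk rather than something the article does. The article nevertheless aims to examine efficacy and prints an MDE at 80% power, so the figure should fit its endpoint and test.

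Finally, the missing square root is typographical. It changes no tabulated value and could have been lost when the text was extracted, so it adds nothing to the main point.

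**Conclusion.** The point holds, and the primary-outcome row of Table 4 is wrong as written. Its MDEs use a baseline SD and correlation that a change-based count cannot have, and an ANCOVA that the plan reserves for secondary outcomes. The planned t-test does not have 80% power at 0.40 (n = 44) or 0.28 (n = 90) for any SD of the improvement count between 1.0 and 2.0.

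How far off the row is depends on an SD that the article does not report. At SD 1.4 the MDE would be about 1.2 at n = 44 and 0.84 at n = 90. Over the assumed SD range it is about 0.86 to 1.73 at n = 44 and 0.60 to 1.19 at n = 90. These figures assume equal arms, two-sided 5% and complete scores for the 44 or 90 participants. The conclusion concerns the stated sensitivity and does not call the design or the choice of test into question.

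**What to change.** 1. State what 5.4 ± 1.4 and 0.94 describe, and remove them as inputs for the primary-outcome row.
2. Recompute that row for the two-sample t-test with the SD of the improvement count. If that SD is not available, show the MDE over SDs of 1.0 to 2.0 (about 0.86 to 1.73 at n = 44), with 1.2 marked as the illustrative value at SD 1.4.
3. When reporting, do not interpret a null result as excluding differences above 0.40 items.
4. As a minor correction, check the footnote formula and add the square root if it is missing in the published version.

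The cost is one recalculated row, some rewording and a less favourable stated sensitivity. The design, sample size and primary test stay as they are.

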If eligibility was probable based on these criteria, the individual was invited to a baseline visit where the research assistants used a scripted guide with clear, concise points to explain the study’s purpose, risks, and benefits, and any answer questions. Participants had the option of having a health proxy in the room during this process. Written informed consent to participate was obtained, including authorization to publish anonymized results as aggregated data. At the baseline visit, interviews and clinical and laboratory measurements were conducted to confirm the cardiometabolic conditions for eligibility, defined as waist circumference ≥94 cm in men or ≥80 cm in women; BMI ≥25 kg/m^2^; measured high systolic blood pressure (≥120 mmHg) or diastolic blood pressure (≥80 mmHg) (or use of blood pressure medication); measured prediabetes (fasting plasma glucose of 100 to 125 mg/dL (5.6 to 6.9 mmol/L) or hemoglobin A1C of 5.7 to 6.4% (39 to 47 mmol/mol); and measured total cholesterol ≥200 mg/dL or triglycerides ≥150 mg/dL or LDL-C ≥130 mg/dL or HDL-C <40 mg/dL, or use of lipid-lowering agents.

Individuals were excluded from the study for several reasons: *1*) self-reported physician-diagnosed type 1 or type 2 diabetes or use of diabetes medication or had a measured fasting plasma glucose ≥126 mg/dL (7.0 mmol/L) or hemoglobin A1C ≥ 6.5% (48 mmol/mol) at the baseline visit; *2*) reported current pregnancy; *3*) reported condition that would influence eating behaviors or nutritional status (e.g., Chron disease, inflammatory bowel disease, celiac disease, liver disease, kidney disease, cancer, diverticulitis, nut allergy, severe food allergies, or aversions); and *4*) intolerance or allergies to legumes (that is, beans and nuts) or vegetable oils (that is, soybean, olive, canola). These exclusion criteria were asked at subsequent visits, and individuals were withdrawn from the study if they answered affirmatively to any of these questions.

The blood test results of potentially-eligible individuals were received within 1 wk of the baseline visit. The values were used to confirm eligibility. If a person was deemed ineligible based on measured laboratory values, the individual was immediately informed and withdrawn from the study. Eligible participants were invited to complete the study examinations and surveys at FDI.

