### Randomization and data collection

Confirmed, eligible, and consented participants were randomly assigned to one of the two study groups (control or intervention) in a 1:1 allocation ratio. These participants were randomized using sex stratification (40% males and 60% females) and permuted blocks with random block sizes. For this randomization scheme, a sequence of block sizes was randomly generated in which allowable blocks were a random mix of sizes 2 or 4 participants. Thus, half of the participants within each block were randomly assigned to the control group and the other half to the intervention group.

Trained research assistants conducted all visits in a single private room at FDI. Research assistants were bilingual (English and Spanish) and trained in culturally sensitive interviewing, clinical protocols, data collection, data entry, confidentiality, and safety measures. Each clinical visit lasted ∼2 h. The counseling session lasted 1 h. Participants were compensated for their time up to $150, such that they received $50 at each of the three examination visits, with no monetary incentive at the counseling session. At the counseling session, participants received a bag with food (intervention group) or cooking utensils (control group). A light, healthy snack, and water were provided after each visit.

Participants were allowed to pause or terminate the interviews at any time. In such case, the participant was contacted up to five times within the subsequent 14 d to complete the pending questionnaires or measurements. Participants remained enrolled in the study for its duration (4 mo) unless they actively left the study, had a new ineligibility factor, or lost contact. All interview questions and outcome measures at 2  and 4 mo were assessed using the same protocols at baseline.

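### Table 4's waist row is labelled cm but fits only inches, so its detectable effect is 2.54 times too small; the HbA1c, glucose, weight and BMI inputs also need checking

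*Protocol article*

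**What the plan says.** Table 4 lists, for each outcome, a baseline mean and SD, a correlation between baseline and 4-month values, and the MDE at two sample sizes. The calculation is described as "using ANCOVA test [101] with 0.05 Type I error and 80% power". A footnote adds: "The results account for 10% loss-to-follow-up for original sample sizes of n = 100 and n = 50".

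The rows at issue are as follows; the table heads the first of them "Waist circumference (cm":

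| Row | Mean ± SD | r | MDE n = 90 | MDE n = 44 |
|---|---|---|---|---|
| Waist, labelled cm | 42.9 ± 4.9 | 0.92 | 1.13 | 1.62 |
| HbA1c (%) | 6.0 ± 1.3 | 0.77 | 0.49 | 0.70 |
| Glucose (mg/dL) | 101.6 ± 29.4 | 0.80 | 10.42 | 14.90 |
| Weight (lb) | 201.2 ± 42.3 | 0.97 | 6.07 | 8.68 |
| BMI (kg/m²) | 34.2 ± 6.6 | 0.86 | 1.99 | 2.84 |

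Under Recruitment, the waist criterion is "waist circumference ≥94 cm in men or ≥80 cm in women". A person is excluded for known or treated diabetes, or who "had a measured fasting plasma glucose ≥126 mg/dL (7.0 mmol/L) or hemoglobin A1C ≥ 6.5% (48 mmol/mol) at the baseline visit". The section on anthropometry records waist in centimetres. The source of the planning means, SDs and correlations is not named.

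**The concern.** Three features of Table 4 do not fit the rest of the article.

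- **Waist.** A mean adult waist of 42.9 cm is not credible beside a mean BMI of 34.2 and cut-offs of 80 and 94 cm.
- **HbA1c and glucose.** Their SDs look too wide for a group from which diabetes-range values are removed.
- **Weight and BMI.** Their correlations differ widely, although in adults BMI is weight divided by a constant for each person.

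The table tells readers what the secondary comparisons can detect, and the Discussion says this pilot will inform larger trials. Someone who took the waist row at face value would expect more than twice the sensitivity that the inputs support. The HbA1c and glucose rows probably err in the other direction.

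**Working it through.** **Inputs.** Two-sided alpha 0.05 ("Two-sided 0.05 type I error threshold for statistical significance will be used"), power 80%, allocation "in a 1:1 allocation ratio", and the Table 4 values above.

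**Reproducing the plan's figures.** With z = 1.960 and 0.842, their sum is 2.8016, and

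MDE = 2 × 2.8016 × SD × √(1 − r²) / √n

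- Waist: 5.6032 × 4.9 × √(1 − 0.92²) = 10.76. Divided by √90 this is 1.13, and by √44 it is 1.62.
- HbA1c: 5.6032 × 1.3 × 0.638 = 4.65, giving 0.49 and 0.70.
- Glucose: 5.6032 × 29.4 × 0.6 = 98.84, giving 10.42 and 14.90.

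All 14 rows reproduce within rounding. The formula printed under the table lacks the square root (without it, waist would be 1.29 and 2.63), but the tabled values were computed with it. Ten per cent loss from 50 leaves 45 rather than 44, which matters little (waist 1.60 against 1.62). The fault is therefore in units and inputs, not in the calculation.

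**Waist.** If the row were in cm, the cut-offs would lie (80 − 42.9)/4.9 = 7.6 and (94 − 42.9)/4.9 = 10.4 SDs above the mean. Read as inches:

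- mean 42.9 × 2.54 = 109.0 cm
- SD 4.9 × 2.54 = 12.4 cm
- MDE 2.88 cm (n = 90) and 4.12 cm (n = 44)

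The table already gives weight in pounds, so an unconverted source is a natural explanation.

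**HbA1c.** For a variable with a fixed mean, minimum and maximum, variance ≤ (max − mean)(mean − min). With mean 6.0 and ceiling 6.5, 1.3² = 1.69 ≤ 0.5 × (6.0 − min) requires a minimum of 2.62% or less. If the minimum is 4.0% (assumption), the largest possible SD is √(0.5 × 2.0) = 1.0. Rounding does not rescue it: mean 5.95 and SD 1.25 still need a minimum of 5.95 − 1.5625/0.55 = 3.1%. A normal distribution with the tabled values puts 35% at or above 6.5%.

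**Glucose.** The same bound needs a minimum of 101.6 − 29.4²/24.4 = 66.2 mg/dL, with values then split between the two extremes. The largest possible SD is 27.8 for a minimum of 70 and 31.9 for a minimum of 60 (both assumptions). This is implausible but not impossible. A normal distribution puts 20% at or above 126.

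**Illustrative MDEs at n = 44.** The eligible-population SDs and the r of 0.5 are assumptions; the other r is the table's own.

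| Outcome | Assumed SD | r | MDE | Stated / this |
|---|---|---|---|---|
| HbA1c | 0.3 to 0.5 | 0.77 | 0.16 to 0.27 | 4.3 to 2.6 |
| HbA1c | 0.3 to 0.5 | 0.5 | 0.22 to 0.37 | 3.2 to 1.9 |
| Glucose | 8 to 15 | 0.80 | 4.1 to 7.6 | 3.7 to 2.0 |
| Glucose | 8 to 15 | 0.5 | 5.9 to 11.0 | 2.5 to 1.4 |

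**Weight against BMI.** The ratio of means is 201.2/34.2 = 5.88 lb per BMI unit. The BMI MDE of 2.84 is then 2.84 × 5.88 = 16.7 lb, against 8.68 lb in the weight row. Assuming equal SDs at both visits, the SD of change is SD × √(2(1 − r)):

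- weight: 42.3 × √0.06 = 10.4 lb
- BMI: 6.6 × √0.28 = 3.49 kg/m², or 20.5 lb

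The two rows imply change SDs that differ about twofold. If the weight row is right, the BMI correlation should be about 1 − (10.36/5.88)²/(2 × 6.6²) = 0.96. If the BMI row is right, the weight correlation should be about 1 − 20.5²/(2 × 42.3²) = 0.88. The document does not show which is wrong.

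**The case against.** **The planning data need not meet the eligibility criteria.** They may come from another study, so a mismatch with the cut-offs alone proves nothing. That is fair in principle, but a mean waist of 42.9 cm with a mean BMI of 34.2 is not credible in any adult sample. For HbA1c and glucose, a different source is exactly the problem.

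**A smaller SD need not mean a smaller MDE.** ANCOVA precision depends on SD × √(1 − r²), and selection on the baseline value lowers SD and r together. Under a linear relation with constant residual variance, the residual SD (0.83 for HbA1c, 17.6 for glucose) and hence the MDE would not change at all. This stands. Better precision requires smaller residual variability in people without diabetes. That is plausible, since an unchanged residual SD of 0.83 would put the 4-month SD well above the assumed baseline SDs of 0.3 to 0.5, but no figure in the article establishes it.

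**Tempting stronger readings.**

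- A reader might infer one common error factor, say 2.5 to 4, across waist, HbA1c and glucose. Only the waist factor follows from the document. The others rest on assumed SDs and correlations, and the directions are opposite.
- A reader might take the planning sample to consist of people the trial excludes. The tabled values put most of that sample below the cut-offs and suggest only that diabetes-range values were included.
- A reader might put 0.97 into the BMI row and quote the result as its correct MDE. The error could equally lie in the weight row.
- A reader might set the waist MDE against the 1 cm improvement threshold. That threshold is an individual change counted in the composite score, whereas the MDE is a difference between arm means.

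**Little depends on these rows.** They concern secondary outcomes of a pilot, and the target was cut from 100 to 50 for budget and timeline. This also stands and limits the severity.

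**Conclusion.** The waist unit error holds. The only inference is that the values are inches, which nothing in the article contradicts. The MDEs in centimetres are 2.88 and 4.12 instead of 1.13 and 1.62, so the row is optimistic by a factor of 2.54.

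The HbA1c SD does not represent the eligible population, provided values as low as about 2.6 to 3.1% are ruled out. The glucose SD is implausible but not excluded. Both MDEs are unreliable and probably too large. The illustrative range of about 1.4 to 4.3 times depends wholly on the assumed SD and r, and is not a correction.

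The weight and BMI rows cannot both be right if they describe the same adults, and the document does not settle which to change.

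This is worth correcting because the table will inform later trials. It does not affect the primary outcome, the sample size or any planned analysis.

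**What to change.** - **Waist:** restate the row as 109.0 ± 12.4 cm, r = 0.92, MDE 2.88 cm (n = 90) and 4.12 cm (n = 44), after confirming that the source is in inches.
- **HbA1c and glucose:** recompute both rows with SD and correlation taken together from people who pass the trial's exclusions. If no such data exist, say so and mark the rows as not representative.
- **Weight and BMI:** check both correlations against the source data and recompute whichever row is wrong.
- **Table notes:** name the source of the planning values, and add the missing square root to the printed formula.

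The cost is a correction to a few table rows and notes, with nothing changed in conduct or analysis. The waist figure becomes less favourable.

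### Table 4's waist row is labelled cm but is almost certainly in inches, so the detectable waist difference at n = 44 is about 4.1 cm, not 1.62 cm

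*Protocol article*

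**What the plan says.** Table 4 of the Protocol article (Statistical Analysis) lists minimum detectable effects for an ANCOVA "with 0.05 Type I error and 80% power". The columns that matter here are headed "MDE for n = 90 (45 per arm") and "MDE for n = 44 (22 per arm"). The row "Waist circumference (cm") shows a baseline mean and SD of 42.9 ± 4.9, a baseline-to-4-month correlation of 0.92, and MDEs of 1.13 and 1.62. The same table gives BMI as 34.2 ± 6.6 kg/m² and weight as 201.2 ± 42.3 lb.

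Elsewhere the article works in cm. The Recruitment section defines elevated waist as "waist circumference ≥94 cm in men or ≥80 cm in women", one of several conditions that can qualify a participant. Primary and secondary outcomes scores a waist item as improved on a decrease of "waist circumference ≥ 1 cm". Anthropometry and blood pressure records waist to the nearest 0.1 cm. No passage says that the Table 4 row is in inches or explains the value 42.9.

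**The concern.** A mean waist of 42.9 cm does not occur in adults, least of all at a mean BMI of 34.2. If the mean is in another unit, the SD probably is too, and the MDEs are computed from the SD. The numbers in the row would then all be false under the printed label.

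Waist is a named secondary outcome, to be compared between arms by ANCOVA. Table 4 exists to tell readers what difference the trial can detect at 80% power. A reader who takes the label at face value will credit the trial with much finer resolution on waist than it has. Anyone who reuses the SD to size a later trial, which the article says this pilot is meant to support, would carry the error forward.

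**Working it through.** **Inputs**
- Two-sided 5% level (Statistical Analysis: "Two-sided 0.05 type I error threshold for statistical significance will be used") and 80% power: z = 1.960 and 0.842, sum 2.802.
- Equal arms (Randomization and data collection: "in a 1:1 allocation ratio").
- Analysed totals of 90 and 44 (Table 4).
- Waist SD 4.9 and correlation 0.92 (Table 4).

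**Step 1: reproduce the printed MDEs.** The right-hand side of the formula printed under Table 4 is the square of the MDE, so its square root is needed:

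MDE = 2 × (1.960 + 0.842) × SD × √(1 − Corr²) / √n

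With √(1 − 0.92²) = √0.1536 = 0.392:
- n = 90: 2 × 2.802 × 4.9 × 0.392 / 9.487 = 1.134 (printed 1.13)
- n = 44: 2 × 2.802 × 4.9 × 0.392 / 6.633 = 1.622 (printed 1.62)

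All 14 rows of Table 4 reproduce to within about 1% in this way. Without the square root, the waist figure at n = 44 would be 2.63, which does not match. The waist MDEs were therefore computed from SD 4.9 and share its unit.

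**Step 2: test the cm label.** Weight of 201.2 lb is 91.3 kg. With BMI 34.2 this implies a height of about √(91.3 / 34.2) = 1.63 m. A 42.9 cm waist is impossible at that size. The article's own waist cut-offs would lie far above the mean:
- women: (80 − 42.9) / 4.9 = 7.6 SD
- men: (94 − 42.9) / 4.9 = 10.4 SD

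**Step 3: test inches.** The mean is 42.9 × 2.54 = 109.0 cm and the SD is 4.9 × 2.54 = 12.4 cm. That mean fits BMI 34.2, and the weight row is also in US units.

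Could only the mean be wrong, with the SD truly in cm? An SD of 4.9 cm around 109 cm is a coefficient of variation of 4.5%, against 6.6 / 34.2 = 19% for BMI and 42.3 / 201.2 = 21% for weight. With mean and SD both in inches it is 4.9 / 42.9 = 11%. The second reading is far more credible.

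**Step 4: MDEs in cm.** Using SD 12.45 cm in the same formula:

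| n | Printed (labelled cm) | Recomputed in cm |
|---|---|---|
| 90 | 1.13 | 2.88 |
| 44 | 1.62 | 4.12 |

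Converting the printed values directly gives 1.13 × 2.54 = 2.87 and 1.62 × 2.54 = 4.11. If the correlation was rounded from anywhere between 0.915 and 0.925, the n = 44 figure runs from 4.24 down to 3.99 cm.

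**Step 5: power at n = 44 for a true difference of 1.62 cm.** The residual SD is 12.45 × 0.392 = 4.88 cm. The standard error of the adjusted difference is 2 × 4.88 / 6.633 = 1.47 cm. Then 1.62 / 1.47 − 1.96 = −0.86, which gives power of about 20%, against the 80% that the table states.

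**The case against.** The strongest reply accepts that the label is wrong and disputes how much follows. Most of it stands.

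- **Sample size and primary outcome.** A reader might infer that the trial was sized on a wrong number. It was not. The section on the impact of COVID-19 says that the target fell from 100 to 50 because of budget and timeline. The composite score has its own row in Table 4, which does not use the waist figures.
- **The 1 cm threshold.** It is tempting to say that the trial can detect only four times its own clinically meaningful waist change. But 1 cm is the within-person change that scores one item as improved, whereas the MDE is a between-arm difference in adjusted means. The two are not the same kind of quantity. Even the printed MDEs of 1.13 and 1.62 exceed 1, so the table never claimed that a 1 cm mean difference was detectable at 80% power.
- **Over-reading a null result.** No passage plans to conclude absence of effect from an MDE. The article calls the trial a pilot and lists its size and short duration as limitations.
- **Mixed units in the trial data.** A reader might infer that inches in Table 4 mean inches in the study database. The documents do not support this, since the measurement protocol specifies cm. The Table 4 baselines may not come from the eligible trial population at all. HbA1c of 6.0 ± 1.3 puts the 6.5% exclusion limit only 0.4 SD above the mean, and glucose of 101.6 ± 29.4 puts the 126 mg/dL limit only 0.8 SD above it. The source is not stated, but separate planning data are plausible.

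What the reply does not remove is a false statement of the difference detectable at 80% power for a prespecified secondary outcome.

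**Conclusion.** The point holds as a unit error in one row. The arithmetic in that row is sound and the label is not. On the inch reading, the detectable between-arm waist difference is about 2.9 cm at n = 90 and 4.1 cm at n = 44, 2.54 times the printed figures.

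This rests on two assumptions. The first is that the unit is inches. The article does not say so, but no other reading fits the BMI and weight rows. The second is that the SD shares the mean's unit, which the coefficients of variation in the same table support. Both can be settled from the source of the planning figures.

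The consequence is limited to how waist is read as a secondary outcome and to reuse of its SD. The design, allocation, primary analysis and sample size do not change.

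**What to change.** Check the unit in the data set from which the Table 4 planning figures were taken. If it is inches, either relabel the row as inches or, for consistency with the rest of the article, convert it to cm: mean 109.0, SD 12.4, MDE 2.9 at n = 90 and 4.1 at n = 44. Interpret the waist comparison, and any later sample-size calculation that uses this SD, against the corrected figures.

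The cost is a source check and one table row. The stated sensitivity for waist becomes less favourable, and no endpoint, analysis or sample size has to be altered.
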